### Sample size and Analyses

The sample size calculation is based on the primary outcome measure, the NDI. The NDI has a clinically important difference of 7/50 (14/100) points for patients presenting a cervical radiculopathy. The standard deviation reported in the literature for this population is 18.4 [33]. The considered parameters are 0,05 for type I error (α) with a power of 0,80 (1-β). For an analysis of variance (ANOVA), the sample size required is 16 subjects per group. However, 18 subjects per group will be recruited to compensate for withdrawals and probable loss of follow-up. This sample size will provide sufficient power to detect a clinically important difference between the two groups.

Descriptive statistics (mean, standard deviation, median frequency counts) will be calculated for all outcome measures at the different times of measurement (week 0, 4 and 8) to summarise results. Baseline demographic data will be compared (independent Student t-tests and Chi-squared tests) across groups to establish the comparability of covariables. If needed, statistical adjustments will be made for baseline characteristics that are significantly different between groups. All data will be tested to ensure they meet the assumptions for the inferential statistical analyses. If they do not meet the necessary assumptions, appropriate non-parametric procedures will be used. An intention-to-treat analysis will be used in which all participants will be analysed in the group to which they were originally assigned. All dropouts and the reason for dropping out of the study will be reported. Any harms or unintended effects during the rehabilitation programs will be recorded, reported and discussed.

A mixed-model, 2-way ANOVA (Groups [experimental program, conventional intervention] × Evaluation [week 0, 4 and 8]) will be used to analyse the effects of the rehabilitation programs. Separate analyses will be conducted on each of the primary (NDI) and secondary (*Quick*DASH, NPRS, cervicothoracic range of motion) outcomes. If an interaction is detected (*P *< 0.05), simple effects will be examined. The Kolmogorov-Smirnov test (*P *< 0.05) will be conducted on the different scores to ensure normality for all variables with significant main effects. For normally distributed variables with significant main effects, post hoc dependent Student *t *tests will be conducted and effect sizes (Cohen's *d*) will be calculated. Effect sizes will be interpreted as small (0.20), medium (0.50), or large (0.80). For any variables that will not be normally distributed, the Wilcoxon signed-rank test and Glass's delta (effect size) will be used for post hoc contrasts. Since this study is looking at a new rehabilitation program, patient's perceived change following the programs will also be categorised as either success or failure. Success will be defined as a 50% improvement in NDI score and a GRC score rated as "moderately better" (+3) or higher. Patients will be classified as failure if the change on the GRC is "somewhat better" (+2) or at any level below this or if there is not a 50% improvement in the NDI [49]. The proportion of success/failure will be compared across groups (Chi-squared tests).

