
Numerous other approaches are commonly utilised in clinical settings, but a formal demonstration of their efficacy remains to be shown. Clinical approaches for cervical radiculopathies commonly include interventions targeting the opening of intervertebral foramen [26]. It is well recognised that cervical movements causing the opening of intervertebral foramen, such as flexion, rotation and lateral flexion contralateral to the nerve root, increase the volume of the foramen, and consequently might decompress a swollen nerve root [27-31]. Inversely, movements of extension, rotation and lateral flexion ipsilateral to the nerve root close the intervertebral foramen around the root. Thus, for acute and sub-acute radiculopathies, intervention programs should include treatment modalities that allow the opening of the intervertebral foramen. On the other hand, movements and positions that lead to intervertebral foramen closure should be avoided. However, no studies have evaluated the effects of a treatment approach that specifically take into consideration these biomechanical principles. Due to the important incapacities related to cervical radiculopathy, and to the few studies pertaining to the efficacy of rehabilitation in this population, we believe in the importance of better understanding the potential of cervical mobilisations and exercises that lead to the opening of the intervertebral foramen. The primary objective of this RCT is to compare, in terms of pain and disability, a rehabilitation program targeting the opening of intervertebral foramen to a conventional rehabilitation program, in patients presenting acute or subacute cervical radiculopathies. Based on biomechanical principles, our hypothesis is that the rehabilitation program targeting the opening of intervertebral foramen will be significantly more effective in reducing pain and disability than the conventional rehabilitation program, mainly at the 4-week evaluation. In considering the passage of time, the differences between the two interventions should be less important at 8-week.

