### Examination procedure and randomisation

After recruitment, the eligible participants will take part in the baseline evaluation. They will complete a questionnaire on sociodemographic, symptomatology and comorbidity, and three self-reported questionnaires on pain and disability: the Neck Disability Index (NDI), the short version of the Disabilities of the Arm, Shoulder and Hand Questionnaire (*Quick*DASH), and a numerical pain rating scale (NPRS). Finally, they will undergo a physical examination of the cervicothoracic spine, which will include the evaluation of cervicothoracic range of motion using a CROM (cervical inclinometers).

After baseline evaluations, assignation of patients to either the conventional or experimental intervention will be performed. To reduce contamination bias, the two programs will be given in different clinics. An independent research assistant will open the randomisation envelope indicating the participant's assignment to the group of clinics that corresponds to the experimental or control group. The research assistant will be blind to the baseline evaluation results and to the assignation of which clinic is providing which intervention. The research assistant will give the list of the clinics providing the rehabilitation program assigned to the participant, and the participant will choose the clinic of their choice. Random number generator will be used to establish randomisation lists prior to the initiation of the study. A member of the research team not involved with data collection will generate the randomisation list. To make sure that two equal groups of 18 subjects will be obtained, blocked randomisation will be used (block size of 6). Three physical therapy clinics will provide the control rehabilitation program and three different clinics the experimental rehabilitation program.

At the end of the 4-week rehabilitation program (maximum 3 days after the last treatment session), and four weeks after the end of the program, the three self-reported questionnaires (NDI, *Quick*DASH, and NPRS), as well as cervicothoracic range of motion will be revaluated. Furthermore, at the two follow-up evaluation sessions, a question pertaining to global change since the initial session (*Global rating of Change *[GRC]) will be completed. An independent physiotherapist, blind to the group assignment, will perform the evaluations according to standardised procedures.

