### Outcome measures (dependent variables)

The NDI questionnaire has been chosen as the primary outcome measure. All evaluations will be undertaken at the CIRRIS. Here is a description of the outcome measures:

*Neck Disability Index: *The NDI is a 10-item questionnaire that measures a patient's self-reported neck pain related disability. Questions include activities of daily living, such as: personal care, lifting, reading, work, driving, sleeping, recreational activities, pain intensity, concentration and headache. The questions are measured on a six-point scale from 0 (no disability) to 5 (full disability). The numeric response for each item is summed for a total score ranging from 0 to 50 [32]. A higher NDI score indicates a greater patient's perceived disability. The reliability (intraclass correlation coefficient [ICC]: 0.73 to 0.98), construct validity, and responsiveness to change have all been demonstrated in various populations [32]. For patients with cervical radiculopathy, the minimal detectable change is 10 points, and the clinically important difference is 7 points [33]. The validated French version of the NDI will be used [34].

*Disabilities of the Arm, Shoulder and Hand: *The *Quick*DASH is a region-specific questionnaire that evaluates the physical disability and symptoms of the upper limb in patients with upper extremity disorders [35]. It consists of 11 items extracted from the original 30-item DASH. Each item has five response choices, ranging from "no difficulty or no symptoms" to "unable to perform activity or very severe symptoms," and is scored on a one-to-five scale. To calculate a *Quick*DASH score at least 10 of the 11 items must be completed. The score ranges from 0 (no disability) to 100 (most severe disability). The validity, reliability (ICC = 0.96) and responsiveness of the *Quick*DASH have been established [36]. The minimal detectable change is 10.8% and the clinically important difference is 10.2% [36]. The *Quick*DASH is also valid for the measurement of upper extremity disability in patients presenting neck pain [37]. The validated French-Canadian version of the *Quick*DASH will be used [38].

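### The stated inputs do not give 16 per group: a two-group comparison with difference 14/100 and SD 18.4 needs 28 to 29

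*Protocol article*

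**What the plan says.** All of the sample size reasoning stands in one paragraph of the protocol article, under Sample size and Analyses.

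- **Difference:** "The NDI has a clinically important difference of 7/50 (14/100) points for patients presenting a cervical radiculopathy".
- **SD:** "The standard deviation reported in the literature for this population is 18.4 [33". No scale is attached to it.
- **Error rates:** alpha 0.05 and power 0.80. Sidedness is not given.
- **Result:** "For an analysis of variance (ANOVA), the sample size required is 16 subjects per group". Recruitment is set at 18 per group to cover losses.
- **Claim:** "This sample size will provide sufficient power to detect a clinically important difference between the two groups".

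No within-person correlation and no baseline adjustment appear among the inputs. The same section plans a mixed ANOVA of 2 groups by 3 evaluations (weeks 0, 4 and 8), with simple effects examined if the interaction is significant. The section on outcome measures scores the NDI from 0 to 50.

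**The concern.** A difference of 14 against an SD of 18.4 is a standardised difference of about 0.76. Detecting that between two groups with 80% power takes well over 16 per group, so the figure looks too small by almost half.

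This paragraph is the only justification for the size of the trial on its primary outcome. If the inputs are taken at face value, a true clinically important difference would be missed in close to half of such trials, while the protocol tells its readers that power is sufficient. The 95% confidence interval would also be wide: at 16 per group its half-width is about 13.3/100, nearly the whole 14-point difference of interest.

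**Working it through.** **Inputs.** All are from Sample size and Analyses: difference 14/100, SD 18.4 (read on 0-100), alpha 0.05, power 0.80. Allocation is 1:1 (Examination procedure and randomisation). Sidedness is not stated; two-sided is the main case because an ANOVA F test has no direction.

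**1. Trying to reproduce 16.**
- Standardised difference: d = 14/18.4 = 0.761.
- Normal approximation: n per group = 2(1.960 + 0.842)²/d² = 2 × 7.849/0.579 = 27.1, so 28.
- Exact noncentral t, identical to a two-group one-way ANOVA: power is 0.798 at 28 and 0.813 at 29, so 29.
- One-sided: 2(1.645 + 0.842)²/0.579 = 21.4, so 22; the exact t gives 23. One-sided power at 16 is 0.68.

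No two-group calculation on the stated inputs alone gives 16.

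**2. What 16 and 18 per group give (two-sided, exact t, one occasion, unadjusted).**

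| Per group | Power for 14/100 |
|---|---|
| 16 | 0.55 |
| 18 (no losses) | 0.60 |

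At 16 per group, 80% power needs d = 1.024. That is a difference of 1.024 × 18.4 = 18.8/100 (9.4/50), or an SD of 14/1.024 = 13.7. The 95% interval half-width is 2.042 × 18.4 × √(2/16) = 13.3/100.

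**3. Where 16 could come from.** A two-sided one-sample or paired t test with d = 0.761 has power 0.78 at n = 15 and 0.81 at n = 16, so it requires exactly 16. That formula addresses change within one group, not a difference between two.

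**4. Whether the planned analysis rescues 16.** Each route needs a correlation ρ that the article does not give. A common SD of 18.4 and equal correlation between visits are assumed.

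- *Group-by-time test, differences 0, 14, 14 at weeks 0, 4, 8.* The noncentrality is (d²/6) × 32/(1 − ρ) = 3.09/(1 − ρ), on 2 and 60 degrees of freedom.

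| ρ | Power at 16 per group |
|---|---|
| 0.5 | 0.57 |
| 0.6 | 0.68 |
| 0.7 | 0.81 |
| 0.8 | 0.94 |

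  The 80% point is at ρ of about 0.70.

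- *Same test, week-8 difference assumed to halve (0, 14, 7).* The Background section expects a smaller difference at week 8; the halving is an illustration, not a figure from the article. The noncentrality is (d²/8) × 32/(1 − ρ), and power at ρ = 0.7 is 0.68.

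- *Baseline-adjusted week-4 comparison.* Replace d by d/√(1 − ρ²). Power at 16 is 0.67 at ρ = 0.5, 0.74 at 0.6 and 0.83 at 0.7; 80% needs ρ of about 0.67.

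- *Group main effect over three visits.* With 14 points at every visit, 80% is reached at ρ of about 0.33 or lower. But that requires a 14-point difference at baseline, where randomisation makes the expected difference zero. With 0, 14, 14 the average difference is two thirds of 14, and power is 0.48 at ρ = 0.3 and 0.40 at ρ = 0.5.

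**The case against.** The strongest defence is that steps 1 and 2 test something other than what is planned. The analysis is a repeated-measures ANOVA, and the article may have dropped a correlation or a software setting that the full protocol holds. Part of this stands. A reader might infer that the true power is 55 to 60%, and the article does not support that: those figures apply to a single-occasion, unadjusted comparison, and the group-by-time test passes 80% at 16 per group once ρ is about 0.70. What the defence does not save is the printed text. It lists its inputs, gives 16 as the result and claims sufficient power from it; at ρ = 0.5 the planned interaction test has power of only 0.57.

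A second tempting reading takes 18.4 on the 0-50 scale on which the NDI is scored. Then d = 7/18.4 = 0.38, about 110 per group are needed, and power at 16 is 0.18. The documents point away from it. The sentence just before the SD converts 7/50 to 14/100, which has little purpose unless the SD is on 0-100. Scores spread evenly over 0-50 would have an SD of 50/√12 = 14.4, so 18.4 would need scores gathered at both extremes. The missing label is a wording defect, not evidence of power below 20%.

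A reader might also infer that a null result is going to be presented as equivalence. Nothing in the article plans that: the hypothesis in the Background section is that the experimental program is superior.

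The directional hypothesis does not rescue the figure either, since a one-sided test still needs 22 to 23 per group.

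**Conclusion.** The concern holds as a failure to reproduce. The inputs printed in the article require 28 to 29 per group for a two-sided two-group comparison, against a stated 16. Rounding or the choice between normal and t formulas moves the answer by one patient, so neither explains the gap.

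The power implied by those inputs alone is about 55% at 16 and 60% at 18 per group. This assumes the SD is on 0-100, two-sided testing, and no gain from repeated measures or baseline adjustment. The actual power of the planned analysis cannot be determined from the article, because it depends on a correlation that is not given. The match with a one-sample or paired formula suggests that a within-group calculation was used, but does not prove it.

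**What to change.** In Sample size and Analyses:

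1. Label the scale of the SD of 18.4; 0-100 appears intended, and the authors should confirm it against their source.
2. Replace the statement of 16 per group at 80% power with one of two versions:
   - what the stated inputs give: at 16 evaluable per group, 80% power for a difference of 18.8/100 (9.4/50), and for 14/100 about 55% power at 16 and 60% at 18; or
   - the named test, its assumed within-person correlation and pattern of differences over time, and the resulting power. For example, the group-by-time test at 16 per group has power 0.57 at ρ = 0.5 and 0.81 at ρ = 0.7 with 14 points at both follow-ups.
3. Delete the sentence claiming sufficient power, or qualify it to match the version chosen.

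This changes wording only and needs no extra patients. The cost is that the stated power becomes less favourable, or comes to rest openly on an assumed correlation.

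### Adjusting only for baseline characteristics that differ significantly picks covariates by chance; prespecify the baseline outcome value instead

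*Protocol article*

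**What the plan says.** The section Sample size and Analyses sets out two linked steps. First, "Baseline demographic data will be compared (independent Student t-tests and Chi-squared tests) across groups to establish the comparability of covariables". Second, with the proviso that this is done only where needed, "statistical adjustments will be made for baseline characteristics that are significantly different between groups". No significance level is given for these tests. The first step speaks of demographic data and the second of baseline characteristics, so it is unclear whether clinical scores such as baseline NDI fall under the rule. No covariate is named on prognostic grounds.

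The same section fixes the main analysis as a mixed-model two-way ANOVA, group by evaluation, in which week 0 is one of three levels of the response and not a covariate. Examination procedure and randomisation describes individual assignment, 18 per group, in blocks of 6, with no stratification factor mentioned. It also states that the NDI is completed at baseline.

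**The concern.** Allocation is random, so any baseline difference between the groups is due to chance. A significance test at baseline therefore examines a null hypothesis already known to be true. Whether a variable belongs in the model depends on how well it predicts the outcome, and the baseline P-value says nothing about that. The rule can bring in an irrelevant variable and leave out a strong predictor with a sizeable but non-significant imbalance.

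Three things are at stake:

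- precision, because a useful covariate is nearly always left out;
- the estimate in the trial actually run, which is shifted when a predictor is moderately imbalanced and not adjusted for;
- prespecification, because the final model is settled only after the data are seen, and the conditional wording of the rule leaves further discretion.

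**Working it through.** **Inputs.** From Sample size and Analyses: "0,05 for type I error (α) with a power of 0,80 (1-β"; "The NDI has a clinically important difference of 7/50 (14/100) points"; "The standard deviation reported in the literature for this population is 18.4"; "the sample size required is 16 subjects per group"; "18 subjects per group will be recruited to compensate for withdrawals and probable loss of follow-up". The SD is read on the 0–100 scale, so the target effect is 14/18.4 = 0.76 SD. Assumptions: two-sided 0.05 for the baseline tests and the main test; covariate–outcome correlation r of 0.3 to 0.7, because the document gives none.

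**The plan's own figure.** n per group = 2 × [(1.960 + 0.842) × 18.4/14]² = 27.1, so 28, not 16. For a simple two-group comparison, power at 18 per group is about 0.60. The 16 would need an unstated correlation (about 0.64 with ANCOVA, or about 0.70 with change scores). That is a separate matter, but it makes lost precision more costly.

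**Size of imbalance that triggers adjustment.** t(0.975, 34) × √(2/18) = 2.032 × 0.333 = 0.677 SD. With 16 per group it is 0.72 SD.

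**How often it triggers.** For one continuous covariate, 5% of randomisations, so 95% have no adjustment for it. For a binary covariate with prevalence 0.3 to 0.5, the chi-squared test triggers in 5.0–6.5% (2.1–2.9% with continuity correction). For at least one of k independent covariates the chance is 1 − 0.95^k: 23% for five, 40% for ten.

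**Shift in the estimate.** An imbalance just under the threshold moves an unadjusted post-treatment comparison by r × 0.677 SD: 0.20, 0.34 and 0.47 SD for r = 0.3, 0.5 and 0.7. Multiplied by 18.4, this is 3.7, 6.2 and 8.7 points out of 100, against a target of 14.

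**Power, covariate outside the model.** Simulation, 18 per arm, one normal covariate, a single post-treatment comparison, true difference 0.76 SD. Always adjusting multiplies the standard error by about √(1 − r²) = 0.95, 0.87 and 0.71.

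| r | Under the rule | Always adjusted |
|---|---|---|
| 0.3 | 0.60 | 0.63 |
| 0.5 | 0.61 | 0.71 |
| 0.7 | 0.62 | 0.86 |

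**Power, baseline NDI.** This variable is already a response level, so the fair comparison is between the planned use of week 0 and its use as a covariate. A change score has standardised effect 0.761/√[2(1 − r)], which is 0.643, 0.761, 0.851 and 0.982 for r = 0.3, 0.5, 0.6 and 0.7. The power column follows from the non-central t with 34 degrees of freedom and non-centrality equal to that effect × √(18/2). The interaction F is simulated with equal correlation between visits and the effect fully sustained to week 8.

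| r | Week-4 change | Interaction F | Week-4 ANCOVA |
|---|---|---|---|
| 0.3 | 0.47 | 0.48 | 0.63 |
| 0.5 | 0.60 | 0.63 | 0.71 |
| 0.6 | 0.70 | 0.73 | 0.78 |
| 0.7 | 0.82 | 0.85 | 0.86 |

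The F test draws on both follow-up visits and the ANCOVA on one, so the last two columns are not a like-for-like comparison. The Background expects a smaller difference at week 8. If the effect halves by then, the F test falls to about 0.51, 0.60 and 0.73 for r = 0.5, 0.6 and 0.7, but that comes from the three-visit omnibus test and not from the adjustment rule.

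**Type I error.** Over all randomisations, the rule with one covariate and a single post-treatment comparison rejects in about 4.8%, 4.3% and 3.5% of null trials for r = 0.3, 0.5 and 0.7.

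**The case against.** The strongest reply is that the planned analysis is not a post-treatment-only comparison. Correlations of 0.5 or more with follow-up NDI are most plausible for baseline NDI, and the group-by-time ANOVA already contains it. This stands. A reader might take the gap of 0.62 against 0.86 as the power lost in the primary analysis; the document does not support that. For baseline NDI at r = 0.7 the gap is 0.82 against 0.86 for week-4 change, and close to nil for the interaction test with a sustained effect. For age and sex a low r is likelier, and the gain is then about 3 percentage points.

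A reader might also infer that no adjustment at all would occur in 95% of trials. That figure is per covariate; with several tested, some adjustment happens more often, though chance decides which.

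Nor does the rule inflate the false-positive rate overall: it is slightly conservative. The rate rises only within subsets. For a covariate outside the model and baseline P between 0.05 and 0.20, about 15% of randomisations, it is near 9% at r = 0.5 and near 12% at r = 0.7. This describes conditional bias and is not a failure of overall error control.

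Finally, a covariate list may sit in an analysis plan that is not shown, so its absence is no finding. The trigger rule, however, is stated outright, and such a plan would have to reverse it.

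**Conclusion.** The point holds in a limited form. The rule selects covariates by chance, makes the model depend on the data, and gives up precision that is available free of charge. The loss ranges from small for weak demographic predictors (about 0.60 against 0.63) to substantial for a strong predictor outside the model, if one exists. For baseline NDI, using week 0 as a response level costs about 16, 11, 8 and 4 percentage points of power at r = 0.3, 0.5, 0.6 and 0.7, comparing the week-4 change contrast with ANCOVA.

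These sizes rest on an assumed r, two-sided 0.05 throughout, the SD read on the 0–100 scale, and 18 per arm with no dropout. The documents do not support saying that baseline NDI imbalance is ignored or that overall type I error is raised. The change is worth making but is no obstacle to the trial.

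**What to change.** Delete the between-group baseline tests and the significance-triggered adjustment, and present baseline characteristics descriptively. Analyse weeks 4 and 8 in a group-by-time model on the post-baseline visits, with the baseline value of the outcome concerned (NDI for the primary analysis) as a prespecified covariate, whatever balance is observed. Add at most one further covariate, named in advance, and only if the investigators can justify it as prognostic.

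The cost is analysis wording and a small change to the planned ANOVA, in which week 0 moves from response level to covariate. Baseline NDI, *Quick*DASH, pain scores and range of motion are already collected, so no new data or participants are needed.

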**Methods/Design:**

This study is a double-blind (participants and evaluators blinded) randomised clinical trial that will allow the comparison of patients with a cervical radiculopathy randomly assigned to one of two groups: one group will receive a 4-week rehabilitation program targeting the opening of intervertebral foramen, and the second group will receive a 4-week conventional rehabilitation program. Thirty-six subjects with cervical radiculopathy will be recruited from participating medical and physiotherapy clinics and will be evaluated at baseline, at the end of the 4-week program and four weeks following the end of the program. The primary outcome measure will be the validated Neck Disability Index questionnaire. Secondary outcome measures will include the short version of the Disabilities of the Arm, Shoulder and Hand questionnaire, a numerical pain rating scale, cervicothoracic mobility and patients' perceived global rating of change. During the 4-week rehabilitation program, each participant will take part in eight physiotherapy treatment sessions (2 session/week) and will perform a home exercise program. A mixed-model, 2-way ANOVA will be used to analyze the effects of the rehabilitation programs.

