## Methods/Design

### Study Design

This double-blind randomised clinical trial will allow the comparison, in terms of pain and disability, of patients presenting a cervical radiculopathy which will have been randomly assigned to one of the two intervention groups: the first group (n = 18) will receive a 4-week rehabilitation program targeting the opening of intervertebral foramen, the second group (n = 18) will receive a 4-week conventional rehabilitation program. Participants will be evaluated on three separate occasions: at baseline (week 0), at the end of the 4-week program (week 4), and four weeks following the end of the program (week 8).

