### Rehabilitation Programs (independent variables)

Physiotherapists working in six physiotherapy clinics in the Quebec City area will provide the rehabilitation programs. Each participant will receive eight physiotherapy treatment sessions during a 4-week span (2 sessions/week; 30 to 45 minutes each session) and will perform a home exercise program. At the beginning of each session, the physiotherapist will conduct a standardised biomechanical examination of the cervicothoracic spine. It will consist of an intervertebral segmental mobility evaluation using lateral glides at the cervical spine and postero-anterior glides at the thoracic spine (T1 to T6). Segmental mobility will be rated as normal, hypomobile or hypermobile. Sandmark & Nisell and Rey-Eiriz et al. demonstrated that this rating of cervicothoracic mobility is sensitive (> 0.80) and specific (> 0.70) [44,45]. Furthermore, this evaluation of segmental mobility is recommended in the *Neck Pain Clinical Practice Guide *of the *American Physical Therapist Association *[5]. The results of the biomechanical examination, as well as the nature and intensity of the intervention, will be documented using standardised forms.

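### The harms sentence covers the 4-week programs, but patients are evaluated and analysed to week 8, so discrete or transient events and co-treatments in weeks 5-8 have no stated record

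*Protocol article*

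**What the plan says.** The only commitment on harms in the protocol article is in Sample size and Analyses: "Any harms or unintended effects during the rehabilitation programs will be recorded, reported and discussed". The preceding sentence there adds that all dropouts and their reasons will be reported, with no time limit.

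Study Design fixes the length of both programs. The experimental group "will receive a 4-week rehabilitation program targeting the opening of intervertebral foramen", and "the second group (n = 18) will receive a 4-week conventional rehabilitation program". The same section sets the evaluations "at baseline (week 0), at the end of the 4-week program (week 4), and four weeks following the end of the program (week 8").

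Examination procedure and randomisation lists what is repeated at both follow-ups: NDI, QuickDASH, NPRS and range of motion. It then adds the global rating of change (GRC): "Furthermore, at the two follow-up evaluation sessions, a question pertaining to global change since the initial session". The analysis text makes week 8 one of the three levels of the evaluation factor in the group-by-evaluation ANOVA.

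**The concern.** Efficacy is followed and analysed over 8 weeks, but the stated harms window closes with the program at 4. A team that follows the sentence as written has no instruction to record an adverse event in weeks 5-8.

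Two things are at stake. The first is that the safety statement would not cover the period over which benefit is reported, in a trial that hopes to inform practice guidelines. The second is the reading of the week-8 result. Prior cervicothoracic surgery, recent cervical injection and current steroid use are exclusions at entry (Participants), so the plan itself treats them as relevant to outcome. If a patient receives one of them in weeks 5-8 and attends week 8 improved, nothing in the article says that this will be known.

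**Working it through.** The plan gives no figure on this point to reproduce. The check is one line of arithmetic and a comparison of sections.

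**Share of follow-up outside the window**

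- Program length: 4 weeks in each arm (Study Design).
- Last evaluation: week 8 (Study Design).
- Share outside = (8 − 4)/8 = 0.50, or 50% of follow-up time.

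**Could the program be read as running past week 4?** The body text says "Each participant will receive eight physiotherapy treatment sessions during a 4-week span" and adds a home exercise program without giving its end date. The abstract places both inside the 4 weeks: "During the 4-week rehabilitation program, each participant will take part in eight physiotherapy treatment sessions (2 session/week) and will perform a home exercise program". Study Design also counts the last four weeks as following the end of the program. The window therefore closes at week 4.

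**What the week-8 visit captures without a harms question**

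- Disability, neck and arm pain, and range of motion are measured again in both arms by an evaluator blind to allocation.
- The GRC runs from −7 to +7 and refers back to the initial evaluation, so deterioration has its own categories.
- A patient who leaves the study because of harm is covered by the dropout reasons.

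**What it does not capture**

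- A transient event. The NPRS asks about pain intensity at the time of asking, and the GRC compares the present state with the initial one. A flare in weeks 5-7 that settles need not appear on either.
- A discrete event outside the content of the scales. Neurological signs are an entry criterion, but they are not among the measures listed for follow-up, so a new deficit would show only indirectly.
- A co-treatment. None of the listed measures records an injection, steroid use or surgery.

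**Consequence for the success outcome.** Success requires a 50% NDI improvement and a GRC of at least +3. The article does not say at which follow-up it is classified. If at week 8, a patient who improved after treatment received elsewhere in weeks 5-8 meets both conditions and counts as a success, with no stated record of that treatment.

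**The case against.** The strongest reply is that this is a journal article. Who asks about harms, when and on which form are details for the full protocol, and the sentence nowhere says that later events will be ignored. Much of this stands: silence on procedure is no fault, and the limit to 4 weeks is inferred from the wording. But the article is not silent on the window. It names one, and that window does not match the follow-up. If the full protocol already records harms to week 8, the sentence needs only to be aligned with it.

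A second reply is that all eight supervised sessions fall in weeks 0-4, so most harms related to treatment may arise there. This also stands. The 50% is a share of calendar time and should not be read as half of the safety information.

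A reader might infer stronger points that the documents do not support:

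- *That late worsening is missed.* It is not. Worsening present at week 8 is measured in both arms.
- *That weeks 5-8 give no harms data at all.* Dropout reasons are reported without a time limit.
- *That harms reporting differs by arm because unblinded therapists at single-arm clinics collect it.* The article never says who records harms, so this is conjecture.
- *That the small sample makes the lost weeks more serious.* With no events in 18 patients, the one-sided 95% upper bound is 1 − 0.05^(1/18) = 15.3%. That bound depends on the number of patients and not on the weeks observed, so it says nothing about the window.

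**Conclusion.** The point holds in limited form. The harms sentence covers 4 of the 8 weeks of follow-up. For patients who still attend, transient or discrete adverse events in weeks 5-8, and injections, steroids or surgery received then, have no stated record.

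The size is modest. The window is the same in both arms, so it does not by itself bias the comparison of harms, and the primary NDI analysis is unaffected. An intention-to-treat comparison remains valid when co-treatments occur. What suffers is the completeness of the safety report and the interpretation of week-8 results, including the success proportion if it is classified at that visit.

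The conclusion assumes that the phrase in the harms sentence means the 4-week program as Study Design defines it, and that no fuller document sets a longer window. How many events would be missed cannot be estimated, because the article gives no event rate.

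**What to change.** Replace the harms sentence with wording to this effect: harms and unintended effects, and any cervical injection, steroid use or surgery, will be recorded from randomisation to the week-8 evaluation and reported by arm, separately for weeks 0-4 and weeks 5-8.

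Collect this with one standard question, identical in both arms and self-completed at the existing week-4 and week-8 visits. Word it so that it does not ask about the mobilisations or exercises received. If the full protocol already provides for this, only the article's sentence needs to be aligned.

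The cost is one sentence, one short form and a few minutes at two scheduled visits. No visit, treatment or sample size changes. Answers could reveal something about allocation to the evaluator, but the risk is small and the self-completed form limits it.
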